### Treatment delivery

The total duration of the treatment period will be 24 weeks. Treatment assignment will be double-blinded. Randomization will be computer-generated and participants will be stratified according to the cause of PAH (idiopathic, heritable, and drug or toxin-induced PAH versus disease-associated PAH) and NYHA/WHO classification (I or II versus III; see Table 3). Participants meeting eligibility criteria for enrollment will be randomized to either 25 mg of spironolactone or matching placebo once daily. The NIH Clinical Center Pharmaceutical Development Section will be compounding and monitoring study drug stability. Four different capsules will be prepared: spironolactone 25 mg and matching placebo, and spironolactone 50 mg and matching placebo. If the 25 mg dose of study drug is well tolerated, (that is, potassium remains <5.0 mEq/L and serum creatinine does not increase >50% from baseline at study entry) then the dose will be increased to 50 mg daily following week 6 laboratory monitoring (Figure 1).

**Figure 1 F1:**
[figure not shown]
**Serum potassium and creatinine monitoring schedule.** *Participants with potassium level ≥5.3 at week 1 will not be eligible for dose increase at 8 weeks. **Throughout the study, participants with potassium level >5.0 will undergo dietary counseling regarding a low potassim diet. Cr, creatinine; K, potassium; labs, laboratory tests.

**Table 3 T3:** New York Heart Association/World Health Organization classification

**Class**	**Symptoms**
I	Patients with pulmonary hypertension but without resulting limitation of physical activity. Ordinary physical activity does not cause undue dyspnea or fatigue, chest pain or near-syncope.
II	Patients with pulmonary hypertension resulting in slight limitation of physical activity. They are comfortable at rest. Ordinary physical activity causes undue dyspnea or fatigue, chest pain or near-syncope.
III	Patients with pulmonary hypertension resulting in marked limitation of physical activity. They are comfortable at rest. Less than ordinary activity causes undue dyspnea or fatigue, chest pain or near-syncope.
IV	Patients with pulmonary hypertension with inability to carry out any physical activity without symptoms. These patients manifest signs of right heart failure. Dyspnea and/or fatigue may even be present at rest. Discomfort is increased by any physical activity.

All participants will receive new study drug in the mail between weeks 7 and 9 of the study. Participants who are not eligible for the dose increase (Figure 1) will also receive new study drug but the dose will be unchanged. The 25 mg and 50 mg dosage formulations will each be a different colored capsule so that the participants and providers can easily discern them. Two different color-matched placebo capsules will be formulated as well. Study coordinators will contact participants and instruct them to begin the new study medication at the appropriate time. Participants will also be instructed to mail their old study medication bottles back to the NIH Clinical Center to avoid confusion with the new study drug.

All participants randomized to either spironolactone or placebo will be counseled on avoiding foods high in potassium and avoiding concurrent use of nonsteroidal anti-inflammatory drugs (NSAIDs). The NIH Clinical Center Pharmacy conducted a formal drug-drug interaction evaluation using Micromedex^®^ (Truven Health Analytics Inc., Ann Arbor, MI, USA), Lexi-Interact™ (Lexi-Comp Inc., Hudson, OH, USA), the package insert for spironolactone, and a focused literature search. No significant interactions were found for spironolactone or any of the PAH-specific drug classes or for HIV antiretroviral therapy. However, phosphodiesterase-5 inhibitors and prostacyclin analogs may enhance the hypotensive effect of any class of antihypertensive medications.

Patients taking potassium supplements at the time of screening will be eligible for enrollment if the primary treating physician and the study investigators believe that it is clinically safe to decrease the current dose or stop the supplement depending on the clinical situation. Potassium will be monitored frequently during this protocol and, if necessary, potassium supplementation can be resumed based on standard clinical practice.

### Protocol procedures

#### Modified New York Heart Association/World Health Organization functional classification of pulmonary hypertension

The modified NYHA/WHO functional classification provides a simple way of classifying the extent of functional impairment in patients with PH [28]. It places patients in one of four categories based on how much they are limited during ordinary physical activity (Table 3).

#### Six-minute walk test

The 6-minute walk test has been used successfully to measure the effectiveness of therapy and risk stratification in heart failure and PH. This test is indicative of an individual’s ability to perform activities of daily living [29,30]. The 6-minute walk test has demonstrated reproducibility in a spectrum of patients with chronic cardiopulmonary disease [30-34]. The coefficient of variance has been reported at <10% [30,32]. As a result, the 6-minute walk test has been accepted by regulatory agencies and is most commonly used as a primary endpoint in randomized clinical trials of PAH-specific therapy [33]. Reference equations for estimating 6-minute walk distance in healthy men and women are based on height, age and weight. In PAH, the distance walked significantly decreases with worsening NYHA/WHO functional class and has been independently related to mortality in PAH by multivariate analysis [35]. The 6-minute walk test will be performed in accordance with standard practice. Each participant will walk along a measured pathway with pulse oximetry and heart rate monitoring. Blood pressure, oxygen saturation, heart rate and a modified Borg dyspnea index will be recorded at baseline, upon completion of the test, and during recovery.

#### Cardiopulmonary exercise testing

Parameters obtained during cardiopulmonary exercise testing, peak oxygen uptake (peak VO_2_) and the slope of ventilation to carbon dioxide production during exercise (VE/VCO_2_) have been well established as powerful prognostic indicators in chronic heart failure. In patients with IPAH, cardiopulmonary exercise testing demonstrated that strong predictors of impaired survival were low peak VO_2_ and low systolic blood pressure at peak exercise [36]. Patients with peak VO_2_ ≤10.4 ml/kg/min and peak systolic blood pressure ≤120 mmHg had poor survival rates at 12 months (23%) compared to patients with one or neither of these risk factors (79% and 97% respectively).

All participants will undergo symptom-limited treadmill exercise testing using a modified Naughton protocol (Table 4). This protocol is designed to gently increase work by limiting each stage increase to approximately one metabolic equivalent (3.5 ml/kg/min VO_2_). The following will be recorded: exercise duration; heart rate, systemic blood pressure and pulse oximetry at the start of the exercise, at the end of each 2-minute stage of the exercise protocol, and immediately after cessation of exercise; and oxygen consumption and carbon dioxide production using breath-by-breath analysis of expired gas (Sensor Medics Horizons MMC, Anaheim, CA, USA) with each 15 seconds of data averaged. Any individual unable to complete the cardiopulmonary exercise testing but otherwise willing to participate in the protocol will remain eligible and their data will be included in any final analyses of the portions of the protocol that they completed.

**Table 4 T4:** Modified naughton protocol for exercise testing

**Stage**	**Time** (**minutes**)	**MPH**	% **Incline**	**METS**
0 (rest/recovery)	1:00	1.0	0.0	1.8
1	2:00	2.0	0.0	2.5
2	2:00	2.0	3.5	3.4
3	2:00	2.0	7.0	4.4
4	2:00	2.0	10.5	5.4
5	2:00	2.0	14.0	6.4
6	2:00	2.0	17.5	7.3
7	2:00	2.6	14.0	8.0
8	2:00	3.0	14.0	9.1
9	2:00	3.4	14.0	10.2
10	2:00	3.7	14.0	11.0

MET, metabolic equivalent (3.5 ml/kg/min VO_2_); MPH, miles per hour.

#### Transthoracic echocardiogram

Echocardiograms will be performed according to standard American Society of Echocardiography criteria using commercially available ultrasound machines. Images will be recorded and saved on an online server. If technically possible, multiple views will be recorded including the parasternal long- and short-axis views, the apical two- and four-chamber views, and the subcostal views. Cardiac chamber sizes will be assessed from multiple views. RV outflow tract flow will be assessed with the sample volume positioned immediately below the pulmonic valve in the parasternal short-axis view with pulse wave and continuous wave Doppler. Analysis of the pulsed wave Doppler signal in the RV outflow tract will allow for measurement of the velocity time integral (surrogate of stroke volume), time to peak velocity (acceleration time) and for categorization of the basic morphology of the Doppler signal (no notch, late systolic notch, mid-systolic notch) [37]. The RV diastolic diameter will be measured 1 cm apical of the tricuspid annulus from the apical four-chamber view. The LV diastolic diameter will also be assessed 1 cm apical of the mitral annulus from the apical four-chamber view. RV end-diastolic dimension can thus be expressed as an absolute value and in relation to LV end-diastolic dimension (RV:LV dimension ratio). Atrial areas will be measured in the same view by planimetry at end-systole. Color Doppler will be used to assess the degree of tricuspid regurgitation in multiple views. The highest right atrial to right ventricular gradient from continuous wave Doppler will be used as an estimate of RV systolic pressure. The spectral jets of tricuspid and mitral regurgitation with continuous wave Doppler will be used for measurement of dP/dt. If technically feasible, subcostal views will be used to assess inferior vena cava size and response to respiratory maneuvers. Tricuspid annular plane systolic excursion will be measured using either M-mode imaging or two-dimensional imaging from the apical four-chamber view [38]. Tissue Doppler imaging will be used for assessment of LV and RV systolic and diastolic performance. Tissue velocity data will be used to derive strain and strain rate measurements for assessment of ventricular systolic and diastolic performance.

#### Magnetic resonance imaging

Assessment of RV structural and functional remodeling remains a fundamental aspect of PAH diagnosis and follow-up [39]. Echocardiography is currently the most commonly used diagnostic tool for these assessments, however, it suffers from many limitations such as limited viewing angles, low signal-to-noise ratio and a low frame rate [40]. Moreover, only longitudinal contraction has been investigated, which represents strain in only one direction and is prone to inaccurate measurements of the RV due to its complex crescent shape [40,41]. RV imaging using MRI has recently gained interest because of the quality and quantity of data obtained with this technique. Unfortunately, assessing changes in global RV structure as well as local contractility still pose difficulties for currently used MRI techniques. Some of these limitations include low functional resolution and prohibitively long image acquisition times in order to obtain three-dimensional contractility data. Our collaborators have recently developed fast MRI techniques for quantification of three-dimensional myocardial strain from single slices [42,43], and for high functional resolution imaging. These new techniques address previous limitations and may allow for a more accurate assessment of RV structural and functional changes and how they evolve with disease progression.

In addition to developing more sophisticated MRI techniques of assessing the RV in patients with PAH, there may also be an important role for using MRI to follow pulmonary artery endothelial function over time and in response to therapy. Currently, much of the interpretation for the role of endothelial function in underlying disease states is based on studies of either peripheral vessel dynamic vasomotor function, which only modestly correlates with that of the main arteries [44-46], or using invasive angiography with Doppler flow measures. MRI is another method of non-invasively assessing arterial cross-sectional area and flow velocity, however, it has been rarely used for endothelial-dependent vasomotor responses [47,48]. Utilizing newer MRI methods, it is now possible to quantify pulmonary arterial vasoreactivity as a surrogate for pulmonary artery endothelial function.

The MRI sequence protocol includes global measures, such as end-diastolic and end-systolic RV/LV volume and RV/LV ejection fractions; local measures, such as RV systolic and diastolic peak longitudinal strain and strain rates and three-dimensional regional contractility (strain) analysis; and vasomotor responses. To assess endothelial-dependent vasomotor responses, each participant will be asked to perform the hand-grip exercise while arterial dimensions and blood flow measurements are obtained [49,50]. Magnetic resonance data will be collected before, during and after hand-grip exercise. The vascular beds of interest include, but are not limited to, the coronary, brachial and pulmonary arteries. Exclusion criteria for MRI and gadolinium are listed in Table 5. Any individual unable to tolerate some or all of the MRI sequences included in the study but otherwise willing to participate in the protocol will remain eligible and their data will be included in any final analyses of the portions of the protocol that they completed.

**Table 5 T5:** Magnetic resonance imaging and gadolinium contrast injection exclusion criteria

**These contraindications include but are not limited to the following devices or conditions:**	
1.	Implanted cardiac pacemaker or defibrillator
2.	Cochlear Implants
3.	Ocular foreign body (for example, metal shavings)
4.	Embedded shrapnel fragments
5.	Central nervous system aneurysm clips
6.	Implanted neural stimulator
7.	Any implanted device that is incompatible with MRI
8.	Unsatisfactory performance status as judged by the physician such that the participant could not tolerate an MRI scan
9.	Participants requiring monitored sedation for MRI studies
10.	Participants with a condition precluding entry into the scanner (for example, morbid obesity, claustrophobia)
11.	Participants with severe back-pain or motion disorders who will be unable to tolerate supine positioning within the MRI scanner and hold still for the duration of the examination
**Exclusion criteria for gadolinium-based MRI studies only:**	
1.	History of severe allergic reaction to gadolinium contrast agents despite pre-medication with diphenhydramine and prednisone
2.	Chronic kidney disease (estimated glomerular filtration rate of <60 mL/min/1.73 m^2^ of body surface area)

#### Plasma assays for markers of endothelial dysfunction and neurohormonal axis assessment

Markers of endothelial dysfunction and neurohormonal assays will be measured using plasma aliquoted from a single 10 mL blood draw collected at the indicated time points (Additional file 1: Figure S1). NT-proBNP testing will be performed on a separate blood sample sent to the NIH Clinical Center Laboratory. A timed 8-hour (overnight) urine sample will be collected, the total volume recorded, and 50 mL will be saved for further processing. Following centrifugation, urine sample aliquots will be stored at −80°C [51]. Plasma and urine aliquots for neurohormonal testing will be shipped to the University of Pennsylvania for further processing.

#### Gene expression profiling of peripheral blood mononuclear cells using Affymetrix GeneChip^®^ Microarrays

PBMCs have repeated contact with the altered endothelial cell surface in PAH and therefore may harbor unique signatures that are indicative of the disease process [52-54]. In a recent pilot study comparing PBMC expression profiles from 10 patients with PAH with 10 age-, gender- and race-matched controls, we identified 321 differentially regulated genes at a 20% false discovery rate. Ingenuity^®^ Pathway Analysis (Ingenuity^®^ Systems, Redwood, CA, USA) identified gene signatures for inflammation, cell-to-cell signaling and interaction, cytoskeletal rearrangement, cellular movement, hemostasis, and cell death [55]. To determine the effects of spironolactone therapy on PBMC gene expression in patients with PAH, we will compare changes in expression profiles at 12 and 24 weeks from baseline (obtained under our Natural History Study) between the treatment and placebo groups.

Blood specimens will be encoded to ensure patient confidentiality. No gene expression information with patient identifiers will be placed in the medical chart or in public records. Total RNA will be isolated, precipitated and quantified. Once total RNA is prepared, samples can be safely stored for an additional year. If longer storage of RNA samples is necessary, a commercially available methodology can be used to safely store total RNA at −80°C for up to 10 years. Total RNA isolated from the patient’s PBMCs will be hybridized to Affymetrix GeneChip^®^ Human Gene 2.0 ST Arrays (Affymetrix^®^, Santa Clara, CA, USA). Expression profile results will be used to direct confirmatory testing using quantitative real-time polymerase chain reaction (PCR).

#### Gene expression profiling of primary pulmonary artery endothelial cells exposed to plasma from participants with pulmonary arterial hypertension

Previous reports have used microarray analysis to PBMCs [52-54] and lung tissue [56,57] from patients with PAH, however a focused investigation of PAH plasma effects on primary human pulmonary artery endothelial cells (PAECs) has not been previously reported to our knowledge [58]. Plasma (from 60 mL of whole blood) will be collected from participants in sterile, endotoxin-free syringes containing heparin. Samples will be collected at baseline (under the Natural History Study) and upon study completion at 24 weeks. This plasma will be used to explore the effects of circulating mediators on PAEC gene expression. We have developed a bioassay assessing global transcriptomic changes in PAECs induced by plasma from patients with PAH compared to healthy controls using Affymetrix^®^ oligonucleotide microarrays. In addition to naive cells, plasma may be tested on PAECs exposed to inflammatory challenges and/or rendered ‘dysfunctional’ (bone morphogenetic protein receptor 2 gene silencing or Smad dominant negative mutant expression with or without endothelial nitric oxide synthase gene silencing). Candidate genes will be confirmed by quantitative real-time PCR. Gene expression changes will be correlated with pulmonary artery endothelial function assessed *in vivo* by MRI as well as with traditional measurements of disease severity, including NYHA/WHO class and 6-minute walk. Remaining stored plasma may later be tested for circulating factors such as microRNAs, cytokines, chemokines or other circulating mediators for correlation with expression profiling results.

### Statistical considerations and analysis of the study

#### Sample size

Previous studies have examined the effects of PAH-specific therapy on time to clinical worsening, exercise capacity and endothelial inflammation in patients with PAH [59-63]. Moreover, the effects of spironolactone on endothelial dysfunction have been examined in diverse non-PAH patient populations [19-23]. However, no prior randomized controlled trials have been completed that report on the effects of spironolactone treatment in patients with PAH. Assuming that a subset of the participants with PAH may discontinue study drug or otherwise not be able to complete the study, we plan to enroll up to 70 participants with PAH to obtain at least 50 completed studies. The participants will be randomized in a 1:1 ratio to spironolactone therapy or placebo. At a two-sided α level of 0.05, we will have at least 84% power to detect an effect size (group mean difference divided by standard deviation) of 0.9 for the difference in the change of 6-minute walk distance from baseline between the two treatment groups [61].

#### Study analysis

Participant characteristics will be summarized using contingency tables (for categorical variables), means and standard deviations for continuous variables that are approximately normally distributed (transformed if needed) or median and inter-quartile range for continuous variables that are not normal.

For the primary endpoints, changes in 6-minute walk distance (24 weeks versus baseline) will be compared between the two groups using linear mixed models (LMMs), Kaplan-Meier curves will be plotted to show the time to clinical worsening, and a log-rank test will be used to compare the two arms. Chi-squared tests or Fisher exact tests, t-tests or Wilcoxon rank-sum tests will be used to compare variables between the two arms when appropriate. The rates of study drug discontinuation between the two arms will be compared using the Fisher exact test, and a logistic regression will be considered to account for potential confounders if the two arms are imbalanced. The causes of discontinuation will be tabulated and compared if appropriate.

For secondary endpoints, LMMs will be used to assess the effect of spironolactone therapy on changes in VO_2_ maximum (24 weeks versus baseline), plasma markers of endothelial inflammation, sex hormone levels, and on activation of the renin-angiotensin-aldosterone and sympathetic nervous systems, as well as RV function as assessed by echocardiography, MRI and NT-proBNP. Random participant effect will be included to account for repeated measures within each participant over time. Transformations (for example, log-transformation) will be considered to stabilize variance. Standard residual diagnostics will be used to assess model assumption. VO_2_ maximum data may not be available for all participants. Based on the recent experience of the NHLBI pulmonary function laboratory at the NIH Clinical Center, approximately 5% to 10% of research participants have been unable to complete cardiopulmonary exercise testing or had incomplete data. We will collect information about the reason for missing VO_2_ maximum data. If the missing data can be considered ‘missing at random’ (for example, due to personal preference, orthopedic issues, inability to tolerate the mouthpiece or facemask), LMM is appropriate. For potentially informative missing data (for example, a participant is too sick to complete the procedure), to be conservative, a minimum value will be used for participants in the spironolactone group, and a last-observation-carry-forward approach will be used in the control group. The proportions of participants in the two treatment groups that have no VO_2_ maximum data will also be compared.

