### Study endpoints

Our primary endpoint is the effect of spironolactone therapy on the change in placebo-corrected 6-minute walk distance at 24 weeks relative to baseline values and the incidence of clinical worsening in the spironolactone group compared to placebo. Clinical worsening will be defined as the addition of a new PAH-specific medication (a prostacyclin, an endothelin-1 receptor antagonist or a phosphodiesterase-5 inhibitor), dose or route escalation (that is inhaled prostacyclin changed to intravenous prostacyclin) of a current PAH-specific medication, development of right heart failure requiring hospitalization or an escalation in outpatient diuretic therapy (that is, initiation of a new diuretic or a dose escalation of current diuretic therapy), transplantation, or death.

Secondary endpoints include effect of spironolactone therapy on exercise capacity, as measured by the change in placebo-corrected VO_2_ maximum at 24 weeks relative to baseline values; effect of spironolactone therapy on plasma markers of vascular inflammation (see Table 2) and peripheral blood mononuclear cell (PBMC) gene expression profiles, comparing changes from baseline between the treatment and placebo groups; effect of spironolactone therapy on sympathetic nervous system activation, renin-angiotensin-aldosterone system activation and sex hormone metabolism, comparing changes from baseline between the treatment and control groups (see Table 2); effect of spironolactone therapy on RV function as assessed by echocardiography, magnetic resonance imaging (MRI) and N-terminal pro-brain natriuretic peptide (NT-proBNP), comparing changes from baseline between the treatment and placebo groups; and safety and tolerability of spironolactone therapy as determined by the rate of study drug discontinuation due to hyperkalemia (serum potassium ≥5.3 mEq/L), renal insufficiency (serum creatinine rise >50% of baseline), or other side effects such as breast pain and gynecomastia compared to placebo.

**Table 2 T2:** Biomarker assessment

**Markers of endothelial dysfunction**	**Neurohormonal axis**
**Adhesion molecules**	**Sympathetic activation**
sICAM-1, sVCAM-1, sE-selectin	Epinephrine, norepinephrine, arginine vasopressin
**Markers of activated coagulation**	**Renin-angiotensin-aldosterone system activation**
von Willebrand factor, thrombomodulin, sP-selectin	Renin activity, aldosterone, angiotensin II, NT-proBNP
**Cytokines and chemokines**	**Sex hormone metabolism**

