### Individual participant stopping rules

PAH is a progressive disease and therefore clinical worsening may occur in participants during the protocol, irrespective of their treatment group assignment. Individual stopping rules for participants enrolled in the protocol include:

1. If a participant develops clinical evidence of right heart failure (which may include but is not limited to elevated jugular venous pressure, ascites and lower extremity edema) as determined by the patient’s primary physician or the investigators, then the participant will be removed from the protocol and treated for decompensated right heart failure according to standard of care.

2. If a participant deteriorates clinically, even in the absence of overt right heart failure, and the primary treating physician or the investigators feel that the addition of a MR antagonist such as spironolactone or eplerenone is clinically indicated then the participant will be removed from the study.

3. If a participant has more than one episode of serious hyperkalemia (potassium ≥5.3 mEq/L) or one episode of severe hyperkalemia (potassium ≥6.0 mEq/L), the study drug will be discontinued and the participant will be removed from the protocol.

4. If a participant develops renal insufficiency (rise in serum creatinine >50% of baseline) while on protocol, then the study drug will be discontinued and the participant will be removed from the protocol.

5. In the event that testing for serum potassium, blood urea nitrogen and creatinine is delayed for >7 days, the participant will be instructed to stop the study drug and will be removed from the protocol.

6. In any participant with a serum potassium level ≥ 5.3 mEq/L, a delay in laboratory monitoring longer than 48 hours from the specified time frame will result in removal from the protocol.

7. If while on study drug a participant develops significant breast pain or gynecomastia then the study drug will be discontinued and the participant will be removed from the protocol.

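### The primary 6-minute walk analysis has no rule for walks missing because of illness or death, so the walk estimate can favour the arm with more failures

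*Protocol article*

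**What the plan says.** All references are to the protocol article.

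- **Study endpoints.** The primary endpoint has two parts: "the change in placebo-corrected 6-minute walk distance at 24 weeks relative to baseline values and the incidence of clinical worsening". Clinical worsening includes "development of right heart failure requiring hospitalization or an escalation in outpatient diuretic therapy", and also transplantation, death and escalation of PAH-specific therapy.
- **Study analysis, primary endpoints.** For the walk, "changes in 6-minute walk distance (24 weeks versus baseline) will be compared between the two groups using linear mixed models". For the other part, "Kaplan-Meier curves will be plotted to show the time to clinical worsening, and a log-rank test will be used to compare the two arms".
- **Study analysis, secondary endpoints.** The missing-data text concerns VO2 maximum. It opens "If the missing data can be considered ‘missing at random", gives personal preference and orthopedic problems as examples, and says that a mixed model then suits. It continues "For potentially informative missing data (for example, a participant is too sick to complete the procedure" and prescribes that "a minimum value will be used for participants in the spironolactone group, and a last-observation-carry-forward approach will be used in the control group".
- **Individual participant stopping rules.** On clinical right heart failure, "then the participant will be removed from the protocol and treated for decompensated right heart failure according to standard of care". The second rule removes a participant who deteriorates, even without overt right heart failure, if a mineralocorticoid receptor antagonist is judged indicated.
- **Overview of study design and study population.** Post-baseline testing is at 12 and 24 weeks.
- **Sample size.** Up to 70 participants are enrolled to obtain at least 50 completed studies.

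**The concern.** The article distinguishes two kinds of missing exercise test: those missed for reasons unrelated to disease course, for which it calls a mixed model appropriate, and those missed because the patient is too sick, which it handles separately. It draws that line for VO2 maximum and not for the walk. Yet the walk is also an exercise test, assessed at the same 24-week endpoint in the same patients, and it is the only outcome with a power statement. The stopping rules take out patients who are doing badly.

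A likelihood-based mixed model uses a removed patient's baseline walk and any week-12 walk, and in effect projects the rest from patients who stayed. A decline after the last observed walk does not enter. If failures are more frequent on one arm, the walk difference is tilted towards that arm. A benefit would be understated if placebo patients fail more, and overstated if spironolactone patients fail more.

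**Working it through.** **1. The design figures are not in question.** With 25 completers per arm, effect size 0.9 and two-sided alpha 0.05, power is 88.9% (normal approximation), 87.7% (noncentral t) or 85.7% (simulated Wilcoxon). The normal approximation with n scaled by the minimum Wilcoxon efficiency, 25 × 0.864 = 21.6 per arm, gives 84.1%. The stated figure of at least 84% is reproduced.

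**2. Room for missing walks.** Planned non-completion is up to (70 − 50)/70 = 28.6%. The article does not say how much of this would be due to worsening, nor how it would split by arm.

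**3. The two endpoints side by side.**

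| | 6-minute walk (primary) | VO2 maximum (secondary) |
|---|---|---|
| Method | mixed model | mixed model |
| Missing for reasons unrelated to illness | nothing stated | mixed model called appropriate |
| Missing because too sick | nothing stated | separate imputation rule |

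The primary endpoint therefore has less stated protection than a secondary one.

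**4. Size under assumptions.** None of these inputs is in the article: 35 per arm, standard deviation of change 60 m, failure rates 20% versus 10%, no effect among patients who do not fail, and a failing patient's week-24 walk lower by a deficit D that earlier visits do not show. The difference between arms in all patients is then

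(0.20 − 0.10) × D = 5, 10 and 15 m for D = 50, 100 and 150 m,

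or 5/60 = 0.08, 10/60 = 0.17 and 15/60 = 0.25 standard deviations, against a design effect of 0.9. Simulation of 1,500 trials per scenario, predicting missing week-24 changes from week-12 changes in observed patients, gave true differences of 5.0, 10.1 and 14.8 m and a model estimate of about 0 m each time. Swapping the arms reverses the sign. For scale, the standard error of a difference with 35 per arm is 60 × √(2/35) = 14.3 m.

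**5. A second set of assumptions.** Here failure is correlated 0.5 to 0.8 with the walk change, and half of the failures also miss week 12. The true effect is 0.9.

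| Failures, placebo / spironolactone | Mixed model | Failures scored at −3 SD |
|---|---|---|
| 10% / 10% | 0.89–0.90 | 0.80–0.81 |
| 5% / 15% | 0.96–1.00 | 0.53–0.57 |
| 15% / 5% | 0.80–0.83 | 1.05–1.09 |

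The direction agrees with step 4. Across all scenarios run, the mixed model moved only 0.00 to 0.15 standard deviations from the effect had everyone walked. The larger gaps to the last column arise because scoring a failure at −3 SD answers a different question.

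**6. Price of a worst-rank analysis.** With 35 per arm, effect 0.9 and failures unrelated to treatment or walk change, simulated power of the worst-rank Wilcoxon test is about 81% with 10% failures per arm and 71% with 15%. A t-test on observed walks has 94% and 92%.

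**The case against.** The strongest reply is that this rests partly on silence. The article never says that the walk is assumed missing at random in patients who die or cannot walk. It is a condensed text, and a full protocol or analysis plan may deal with the matter. The VO2 maximum rule also has a test-specific reason: 5% to 10% of that laboratory's research participants could not complete cardiopulmonary testing or had incomplete data. And the article says that a mixed model is appropriate if data are missing at random; it does not say only then. All of this stands. What remains is not silence alone: the article spells out the distinction for a secondary endpoint, names one method for the primary one, and prints stopping rules that remove the sicker patients. Whether removed participants would still return for a week-24 walk is not stated.

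A reader might infer that the analysis discards the failures, or that harm from spironolactone would be hidden. The documents do not support either reading. The mixed model keeps baseline and any week-12 walk. Death, transplantation and right heart failure that leads to hospitalization or more outpatient diuretic are clinical-worsening events compared by log-rank, and serious adverse events are monitored by treatment group. The limitation belongs to the walk estimate, which the log-rank test does not correct.

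It is also fair that the 5 to 15 m follows directly from the assumed rates and deficits, and is about one standard error or less.

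**Conclusion.** The point holds for the walk estimate and not for the trial as a whole. The stated method does not reflect walks missing because of illness or death, although the article itself regards that reason as potentially informative for another exercise test. The bias favours whichever arm has more failures. Its size cannot be derived from the article. Under the assumptions in step 4 it is about 5 to 15 m, or 0.08 to 0.25 standard deviations; with equal failure rates and equal deficits in the two arms that calculation gives none. The stated power is not in error, and the mixed model need not be replaced. This is a cheap improvement to make while the trial is still recruiting.

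**What to change.** Keep the mixed model as the primary estimate. Add to the primary-endpoint paragraph of Study analysis a prespecified sensitivity analysis along these lines:

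*Week-24 walks missing because of death, transplantation, right heart failure or being too ill to walk will receive the worst ranks, by the same rule in both arms. The arms will be compared with a Wilcoxon test stratified by the randomization factors (cause of PAH and functional class). Any discordance with the mixed model will be reported when the walk result is interpreted.*

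The VO2 maximum rule should not be copied to the walk, because it imputes differently in the two arms.

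The cost is one paragraph, with no new visits; the reason for each missing walk must be recorded. There are three downsides. The rank analysis gives no estimate in metres. It has lower power when failures are unrelated to treatment (step 6). It also counts events that already enter clinical worsening. For these reasons it should be a sensitivity analysis, and not a condition for claiming benefit.
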